#### **Study procedures**

The study team will visit the selected households and brief them about the survey objectives and process involved. After obtaining consent, information on basic demographic details, exposure history to laboratory-confirmed COVID-19 cases, symptoms suggestive of COVID-19 since March 2020, clinical history, COVID-19 testing and COVID-19 vaccination details will be recorded. All data will be entered in an Open Data Kit (ODK) application on mobile phones by the survey teams.

Trained phlebotomists in each survey team will collect 3 ml of venous blood from each participant. The serum will be separated after centrifugation in a local health facility and transported to the ICMR-NIE laboratory in Chennai.

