### **Analysis plan**

#### **A] General population**

We will calculate the frequency of characteristics of survey participants. The reported occupations will be categorised into high and low risk considering the potential risk of exposure to known or unknown COVID-19 case.

We will estimate the seroprevalence of SARS-CoV-2 infection along with 95% confidence intervals using appropriate sampling weights and considering the cluster sampling used for the survey. We will define an antibody positive case as an individual whose sera tested positive on either of the two assays. Hence the sero-prevalence estimated will be based on presence of either N antibodies or S1-RBD antibodies. The final prevalence estimates will be calculated after adjusting for the IgG test performance characteristics of both assays.

We will use the survey data analysis module in STATA software (StataCorp LLC, Texas, USA).

We will separately estimate the seroprevalence of infections only among the adults. In order to maintain comparability with the previous surveys, we will randomly select one adult survey participant per household from the survey database.

We will estimate proportion of individuals with COVID-19 vaccination along with 95% CI. We will also estimate the seroprevalence with 95% CI for SARS-CoV-2 infection by age, sex, locality, occupation, symptom status, contact history, RT-PCR testing and confirmation status.

We will estimate the infection-to-case ratio as the number of individuals with SARS-CoV-2 infection (as per IgG detection) compared to the number of RT-PCR reported cases of COVID-19. We will apply the seroprevalence to the total population above 10 years projected for the year 2020 using 2011 census data to estimate the number of infections in the country. The published literature indicates that the IgG antibodies against SARS-CoV-2 infection start appearing by the end of first week, and most cases are IgG positive by the end of the second week (10). We will consider the number of reported COVID-19 cases 15 days and one week before the initiation of serosurvey to estimate the plausible range of the number of infections. We will estimate the range of the infection fatality ratio (IFR) assuming a three-week lag time from infection to death (11,12)

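### The stated range for the infection-to-case ratio reflects only two case-count dates and does not carry in the survey's sampling error, so it would be too narrow

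*Combined protocol and SAP*

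**What the plan says.** In the Analysis plan, A] General population, the infection count is built as follows: "We will apply the seroprevalence to the total population above 10 years projected for the year 2020 using 2011 census data". The result is a single national count. That count is then "compared to the number of RT-PCR reported cases of COVID-19". On uncertainty, the plan says: "We will consider the number of reported COVID-19 cases 15 days and one week before the initiation of serosurvey", to give a plausible range. The sentence attaches this range to the number of infections, but the quantity that changes with the date is the reported-case count, so I read it as the range for the ratio. The infection fatality ratio is also to be given as a range, with a three-week lag from infection to death.

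The same section plans seroprevalence "along with 95% confidence intervals using appropriate sampling weights and considering the cluster sampling used for the survey", and a 95% interval for vaccination coverage. No interval is mentioned for the ratio.

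Participants' own testing is available: under Study procedures, "COVID-19 testing and COVID-19 vaccination details will be recorded". Under Sampling method, people with an earlier RT-PCR or antigen confirmation stay eligible. The plan uses this information only to break seroprevalence down by "RT-PCR testing and confirmation status".

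**The concern.** The ratio has a survey estimate on top and an administrative count underneath. Moving the case-count date changes only the lower part. The upper part has sampling error that the plan already intends to estimate, but nothing says it will reach the ratio. A reader given the two-date range would reasonably take it as the full uncertainty. The same applies to the infection fatality ratio, which uses the same infection count.

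A lesser point is that the survey holds data for a second, independent look at case ascertainment, and the plan does not use them that way.

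**Working it through.** **Inputs from the documents.** Sample size section: prevalence 30%, relative precision 10% (so d = 0.03), design effect 2; 19,600 adults + 5,600 aged 10–17 = 25,200 aged 10 and over; 28,000 in all. Introduction: round 3 seroprevalence 24.1% (23.0–25.3); about 25 million reported cases by 29 May 2021.

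**Assumptions not in the documents.** Projected population above 10 years, 1.1 billion; cumulative reported cases at the later date, 28 million; new cases per day, 50,000 to 200,000; share of participants with a confirmed history, 0.5% to 3%.

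**1. The plan's own figure.** n = DEFF × 1.96² × p(1−p)/d² = 2 × 3.8416 × 0.21/0.0009 = 1,792.7. The stated 1,792 for ages 6–9 reproduces, so the same variance formula is used below.

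**2. Sampling error of the numerator.** With the population and case count treated as fixed, the ratio inherits the relative error of seroprevalence, 1.96 × √(DEFF × p(1−p)/n)/p.
- DEFF 2: 1.96 × √(2 × 0.21/25,200)/0.30 = 0.0080/0.30 = ±2.7%.
- DEFF 4: ±3.8%.
- Round 3 as observed: (25.3 − 23.0)/2 = 1.15; 1.15/24.1 = ±4.8%. With 28,000 participants assumed for that round, this implies a design effect of (0.0115/1.96)²/(0.241 × 0.759/28,000) = 5.3.
- If prevalence were 60%, the error would fall to ±1.4% (DEFF 2) or ±2.0% (DEFF 4).

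**3. Width of the two-date range.** The dates are 15 − 7 = 8 days apart. 8 × 50,000 = 0.4 million and 8 × 200,000 = 1.6 million. Over 28 million this is 1.4% to 5.7% in total; over 25 million, 1.6% to 6.4%. The full width of the sampling interval is 2 × 2.7% = 5.3% (from the unrounded 2.67%) to 2.3/24.1 = 9.5%.

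**4. Both together.** Infections = 0.30 × 1.1 billion = 330 million. The lower limit uses 28 million cases and the upper limit the earlier count.

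| Earlier count | Dates only | With ±2.7% | With ±4.8% |
|---|---|---|---|
| 27.6 million | 11.8–12.0 | 11.5–12.3 | 11.2–12.5 |
| 26.4 million | 11.8–12.5 | 11.5–12.8 | 11.2–13.1 |

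Under these assumptions the combined range is about 2 to 8 times as wide as the dates-only range.

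**5. Is a within-survey ratio feasible?** Let p be the share positive and c the share reporting confirmation, with confirmed people treated as a subset of positives. Then Var(log p/c) = DEFF × (1/(nc) − 1/(np)). With p = 30%, DEFF 2, n = 28,000:
- c = 2% (560 people): 2 × (1/560 − 1/8,400) = 0.00333, giving 15 (13.4–16.8). Adults alone: 15 (13.1–17.2).
- c = 1% (280 people): 30 (25.5–35.3).
- c = 0.5% (140 people): 60 (47.6–75.7). Ages 6–9 would have 14 confirmed participants and 60 (28.8–125).

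It is usable overall and for adults, but not dependable for the youngest group.

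**The case against.** The strongest reply is that this is only a reporting gap. The numerator already has a planned 95% interval, and dividing by a fixed count rescales it, so any analyst could supply the missing interval. The omitted error is a few percent, and the ratio is not among the survey's objectives. Both stated objectives concern antibody prevalence, and the expected benefits do not name the ratio. All of this stands and limits the importance of the point. It does not remove it, because the plan names a range and that range leaves out a source of error of similar or larger size.

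Three stronger readings are tempting, and the documents do not support them.
- A reader might infer that the ratio has no sampling error. It has; the plan is silent on carrying it through.
- A reader might infer that the ratio cannot be split by age or locality. The plan does not split it, but seroprevalence is planned by both, and nothing says whether reported cases are available by those groups.
- A reader might take the within-survey ratio as a clean matched check. It is not. Test history appears to be taken at interview; home-isolated cases are excluded and deaths are not captured; confirmation includes antigen tests whereas the planned ratio names RT-PCR; and the survey enrols from age 6 whereas the planned ratio uses the population above 10. Positivity on either assay can also reflect vaccination, since the introduction describes antibodies as natural and vaccine-induced and reports 160 million people with at least one dose. Both ratios share that numerator, so agreement between them would not confirm the infection count.

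**Conclusion.** The point holds as a modest defect in the stated uncertainty. The range for the infection-to-case ratio reflects case-count timing only. It omits a relative sampling error of about ±2.7% (plan assumptions) to ±4.8% (round 3), against a two-date span of about 1.4–5.7% in total. The first figure rests on 30% prevalence and a design effect of 2 and would be smaller at higher prevalence. The second assumes this round clusters much as round 3 did. The two-date span rests wholly on assumed case counts.

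The plan shows no arithmetic error here and the primary estimates are unaffected. The absence of a within-survey ratio is a missed opportunity, not a fault.

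**What to change.** In the Analysis plan, A] General population, state that the infection-to-case ratio will be computed at the lower and upper limits of the design-based, assay-adjusted seroprevalence 95% interval for each of the two case-count dates, and that the combined range will be reported. Do the same for the infection fatality ratio, since it uses the same infection count. Describe the result as a range over dates and sampling error, not as a 95% confidence interval, and note that the projected population is treated as fixed. The cost is a few lines of calculation and a wider stated range.

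Optionally, add a survey-weighted ratio of antibody-positive participants to participants reporting a confirmed infection, with a design-based 95% interval, overall and for adults. It is best shown also among unvaccinated participants, and restricted to RT-PCR confirmation and to the age range of the external ratio. Label it a cross-check limited by self-report, by the absence of home-isolated and deceased cases, and by vaccine-induced positivity. State in advance that a difference between the two ratios will not be read as under-ascertainment alone. The variables are already collected, so the cost is some survey-analysis code. The restrictions will reduce the number of confirmed participants and widen the interval.

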## **Population-based serosurvey to estimate prevalence of SARS-CoV-2 antibodies in India: Fourth survey, June - July 2021**

India is witnessing a second wave of SARS-CoV-2 infections from February 2021, spread across majority of states of India (1). As of May 29, 2021, India had reported around 25 million cases and more than 3,00,000 deaths (2). The first round of national serosurveillance was conducted from May 11, 2020, to June 4, 2020, among adults in randomly-sampled 700 clusters selected from 70 districts of 21 Indian states. The population-weighted seroprevalence after adjusting for test performance was 0.73% (95% CI: 0.34-1.13). The second round of nationwide serosurvey was conducted between 17 August and 22 September 2020 among individuals aged 10 years and above in the same clusters from 70 districts of 21 states (3). The findings indicated an overall seroprevalence of around 7%, with a ten-fold rise in adult prevalence between May and August 2020. It also indicated a substantial transmission in rural areas with the seroprevalence continuing to be higher in urban slum and non-slum areas (4).

ICMR conducted the third population-based serosurvey among individuals aged 10 years and above and health care workers between Dec 18, 2020 and Jan 6, 2021 in the same 700 villages or wards from 70 districts in 21 states selected for the first and second serosurveys. In the third serosurvey, prevalence was estimated based on the presence of both IgG antibodies against SARS-CoV-2 S1 protein of the receptor binding domain (S1-RBD) and nucleocapsid (N) protein of SARS-CoV-2 while in second serosurvey prevalence was based on IgG antibodies nucleocapsid (N) protein of SARS-CoV-2. The weighted and assay characteristic adjusted seroprevalence among general population was 24.1 (95%CI: 23.0% to 25.3%) The survey indicated that three fourth of the population were still susceptible and a higher sero-prevalence of SARS-CoV-2 infection in urban areas compared to the rural areas (5). Apart from the nationwide serosurveys, several cities and states conducted serosurveys. Metropolitan cities like Delhi, Mumbai, Pune, Chennai, Ahmedabad, Hyderabad have reported seroprevalence ranging between 17.6% and 56% at different timepoints (5).

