India started COVID-19 vaccination with BBV152 vaccine (Covaxin; Bharat Biotech) and ChAdOx1 nCoV-19 vaccine (COVID-19 Vaccine AstraZeneca) since January 16, 2021 under Emergency Use Authorization for the health care workers. The vaccination strategy was expanded for frontline workers in February 1, 2021 for frontline workers. In Phase 2 individuals above 60 years old and above 45 years old with specified comorbidities

became eligible for vaccination from March 1, 2021 followed by Phase 3 for all above 45 years of age from April 1, 2021. And finally Phase 4 for all above 18 years of age began on May 1, 2021 (6). Around 44 million individuals have received two doses while 160 million have received at least one dose of vaccine as on May 29, 2021 (7).

Population-based sero-epidemiological studies measure the presence of antibodies against SARS-CoV-2 (natural and vaccine induced) in different age groups. Repeated cross sectional serosurveys conducted in the same geographical location provide estimates to monitor trends over a period of and provide information valuable for the public health decision makers to design and revise containment strategies (8). The earlier serosurveys were conducted among individuals aged 10 years and above and seroprevalence among children below 10 years is still unknown. SARS-CoV-2 poses a high occupational risk to healthcare workers who are at the forefront of managing COVID-19 cases in hospital settings. The third serosurvey indicated seroprevalence around 25% among the HCWs. Also, the HCWs were prioritised for COVID-19 vaccination in the first phase of vaccine rollout in India owing to higher risk of exposure to infected persons.

In this context, it is proposed to conduct fourth round of serosurveillance to determine the prevalence of SARS-CoV-2 antibodies in the community and health care workers as per change in epidemiology and public health response to the epidemic in the country.

The objectives of the fourth survey are:

1. Estimate the prevalence of SARS-COV-2 antibodies among (a) children aged 6-17 y and (b) adults in the general population, at the national level
2. Estimate the prevalence of SARS-COV-2 antibodies among healthcare workers at the national level

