### **Study population**

A] General Population

Inclusion criteria: Usual resident, age  $\geq 6$  years, available at the time of the household visit and willing to participate

Exclusion criteria: Age < 6 years; locked household; guest/visitor; not willing to participate

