### **Sample size**

#### A] General population

We plan to enrol 28,000 individuals (19,600 individuals in the age group  $\geq 18$  years, 5600 children in the age group of 10-17 years and 2,800 children in the age group of 6-9 years) across the country by allocating a minimum of 400 individuals to each of the 70 districts that were included in the earlier survey. We have divided the overall sample size of 28,000 in the above-mentioned age groups as per age structure of the population (Census 2011).

The sample size assuming a seroprevalence of 30%, with 10% relative precision, for 95% CI and design effect of 2 would be 1792 for children in the 6-9 age group. The required sample size is sufficient to estimate prevalence for each age group. However, in order to have a sufficiently large sample for a national level survey, we will keep the same overall sample size for the fourth serosurvey.

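### The infection total uses the 2020 population above 10 years, although the survey enrols from age 6 in mid-2021, so the sampled 6-9 year olds are left out

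*Combined protocol and SAP*

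**What the plan says.** The Analysis plan for the general population gives this rule for the number of infections: "We will apply the seroprevalence to the total population above 10 years projected for the year 2020 using 2011 census data". The result is described as a count for the whole country. The same paragraph plans an infection-to-case ratio against RT-PCR reported cases and an IFR with a three-week lag to death. It states no age limit for cases or deaths.

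Other sections describe a different population and date:

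- The title dates the survey: "Fourth survey, June - July 2021".
- The only age exclusion in Study population, A] General Population, is below 6 years: "Exclusion criteria: Age < 6 years; locked household; guest/visitor; not willing to participate".
- Objective 1 covers "children aged 6-17 y and (b) adults in the general population, at the national level".
- Sample size, A] General population, includes "2,800 children in the age group of 6-9 years" in a total of 28,000, and says the split follows the Census 2011 age structure.

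The introduction explains why the younger children were added: "The earlier serosurveys were conducted among individuals aged 10 years and above and seroprevalence among children below 10 years is still unknown".

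**The concern.** A cut-off at 10 years and a 2020 base year fit the second survey, which the introduction places in August-September 2020 among people aged 10 and above. They do not fit this one. No section gives a reason for keeping either.

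The infection total is the numerator of the infection-to-case ratio and the denominator of the IFR. If it omits an age group while the case and death counts do not, the ratio is too low and the IFR too high. The shortfall is systematic: a larger sample does not reduce it, and the confidence interval for prevalence does not show it. A reader of the report would also take a national count to include the children this round was extended to cover.

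**Working it through.** **The plan's own figures.** The plan gives no infection total to reproduce. The figures it gives for the omitted group do reproduce:

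- Allocation: 70 districts x 10 clusters x 40 people = 28,000; aged 6-9: 70 x 10 x 4 = 2,800.
- Required sample at 6-9 (prevalence 0.30, relative precision 0.10, 95% confidence, design effect 2): 2 x 1.96² x 0.70 / (0.30 x 0.10²) = 1792.7, against 1792 stated. The planned 2,800 exceeds this, so a separate 6-9 estimate is available at the planned precision under those inputs.

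**Inputs.**

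- s = share of the 6+ population aged 6-9 = 2,800/28,000 = 0.10 (Sample size). This is a rounded quota of 7:2:1 per location (Sampling method), so 0.08-0.12 is also tried.
- r = prevalence at 6-9 divided by prevalence at 10+. Not in the documents; assumed 0.5-1.25.
- g = population growth from 2020 to 2021. Not in the documents; assumed 0.5-1.5%.
- The plan's age limit is read as 10 and over. Read strictly, it would also drop 10-year-olds and widen the gap slightly.

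Let N be the 6+ population and p the prevalence at 10+. The 6+ prevalence is P = p[(1 - s) + s r], and the 6+ total is T = N P.

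**Reading A: the 6+ prevalence is applied.** The planned total is P x N(1 - s), so planned/T = 1 - s = 0.90, whatever r is. With s = 0.08 it is 0.92; with s = 0.12 it is 0.88. For scale, per 1 billion people aged 6+ (a round illustrative figure) at the planning prevalence of 30%: 0.30 x 0.90 = 270 million counted, against 300 million.

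**Reading B: a 10+ prevalence is applied.** The planned total is p x N(1 - s), so planned/T = (1 - s)/[(1 - s) + s r]. With s = 0.10:

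| r | planned/T |
|---|---|
| 0.5 | 0.90/0.95 = 0.947 |
| 0.75 | 0.90/0.975 = 0.923 |
| 1.0 | 0.90/1.00 = 0.900 |
| 1.25 | 0.90/1.025 = 0.878 |

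**Base year.** The factor is 1/(1 + g): 1/1.005 = 0.995 to 1/1.015 = 0.985. Combined with reading A: 0.90/1.005 = 0.896 to 0.90/1.015 = 0.887.

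**Effect on the ratio and IFR.** For fixed case and death counts, the infection-to-case ratio is multiplied by planned/T and the IFR by its reciprocal. At 0.90, the ratio is multiplied by 0.90 and the IFR by 1/0.90 = 1.11. These factors are relative to values based on the 6+ total.

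**If cases and deaths were limited to ages 10 and over.** The matching total is p x N(1 - s). Apart from the base year, reading B then has no error. Under reading A the total is (1 - s) + s r times the matching one: 0.95 at r = 0.5 and 1.025 at r = 1.25. The error is at most about 5%, and its direction can reverse.

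**The case against.** The strongest reply is that the plan may intend a 10+ prevalence. Seroprevalence by age is already planned, so that estimate will exist. Applied to a 10+ population it gives a coherent count, comparable with surveys 2 and 3. This stands in part. A reader might infer that the plan definitely applies a prevalence including 6-9 year olds to a population excluding them, but the text does not settle this. It does not clear the rule, however: a 10+ count is still not a national one and still omits children the survey samples. The plan states comparability with earlier rounds as the aim of the one-adult-per-household analysis, not of this calculation.

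Second, a reader might infer fixed errors, such as a ratio about 11% too low and an IFR about 12% too high. The documents do not support single figures. Those need a 6+ prevalence, a growth rate near 1%, and the 6+ total as the right match for the case and death counts. If the counts cover all ages, the matching total would also include under-6s, whom the survey does not measure. If they cover ages 10 and over, the age error is small or absent.

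Third, the net direction is not established. Positivity on either assay is counted as infection, while the introduction notes that antibodies may be vaccine-induced and reports 160 million people with at least one dose. That pushes the infection count up. It is a separate matter, but the factors above hold only with all else equal.

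Finally, neither the infection total, the ratio nor the IFR is a listed objective, and the error can be corrected after data collection. This is right and limits the weight of the point.

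**Conclusion.** The point holds, and the rule should be corrected before analysis. As written, the infection total omits the 6-9 year olds on either reading of the prevalence and uses a population one year out of date. The age limit is the main fault; the base year is minor and omits no age group.

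Against a 6+ total, the age shortfall is 10% with the 6+ prevalence (8-12% if the share differs as assumed), or about 5-12% with a 10+ prevalence over the assumed range of r. With the 6+ prevalence, the two quantities multiplied also cover different age ranges. No exact error for the ratio or IFR can be given until the plan states the ages covered by cases and deaths.

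A reader might infer that the survey's main results are compromised. They are not: the prevalence estimates for children, adults and healthcare workers do not use this multiplier.

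**What to change.** Replace the rule in the Analysis plan, A] General population, as follows:

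- Multiply age-specific seroprevalence (6-9, 10-17, 18 and over) by the matching age-specific populations projected for 2021, and sum.
- Label the result as infections in the population aged 6 and above.
- Restrict cases and deaths to age 6 and above where age is available; otherwise state that all-age counts are used.
- Report a 10+ total separately, as 10+ prevalence times 10+ population, for comparison with surveys 2 and 3.

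The cost is obtaining 2021 age-specific projections, looking for an age breakdown of cases and deaths (the documents identify no source for either), and a little more analysis. No extra fieldwork or testing is needed, because the 6-9 sample and the by-age estimates are already planned.

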### **Sampling method**

#### A] General population

We will select 10 clusters (villages in rural areas and wards in urban areas) for each of the district by Probability proportional to size sampling. In each of the selected village/ward, we will select four random locations. In each location, the survey team will choose a random start household and visit consecutive households until 7 individuals from age-group  $\geq 18$  years, 2 children in the age group of 10-17 years and 1 child in the

age group of 6-9 years are enrolled. All household members, 6 years and older, will be included. Within each cluster, 40 individuals (28 individuals from  $\geq 18$  years, 8 children in the age group of 10-17 years and 4 children in the age group of 6-9 years) will be included for the survey. Individuals with history of laboratory confirmed SARS-CoV-2 infection by RT-PCR and/or rapid antigen test will not be excluded. SARS-CoV-2 cases in home isolation will not be included in the survey.

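### The plausible range for infections is taken from case-count dates that cannot produce it; survey error is not carried into infections, ICR or IFR, and the case count is dated too early and defined inconsistently

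*Combined protocol and SAP*

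**What the plan says.** The text is in the Analysis plan, A] General population, of the combined protocol and SAP.

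- **Seroprevalence** gets a 95% CI that allows for weights and clustering, and is adjusted for assay performance.
- **Infections:** "We will apply the seroprevalence to the total population above 10 years projected for the year 2020 using 2011 census data". No interval is mentioned at this step.
- **ICR:** infections are "compared to the number of RT-PCR reported cases of COVID-19".
- **Range:** "We will consider the number of reported COVID-19 cases 15 days and one week before the initiation of serosurvey to estimate the plausible range", and the stated purpose in full is "to estimate the plausible range of the number of infections".
- **IFR:** "We will estimate the range of the infection fatality ratio (IFR) assuming a three-week lag time from infection to death". The end points of that range and the date up to which deaths are counted are not given.

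The Sampling method, A] General population, describes prior infection differently from the ICR sentence: "Individuals with history of laboratory confirmed SARS-CoV-2 infection by RT-PCR and/or rapid antigen test will not be excluded".

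**The concern.** The plan attaches a range to a quantity that its source of variation cannot affect. It does not say how the uncertainty it does measure, the design-based CI, reaches the derived figures. An analyst who follows the text literally would report infections, ICR and IFR with ranges that contain no sampling error.

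Two further features affect the ICR itself. The case count is fixed relative to the first day of the survey, while antibody status refers to the day each participant's blood is drawn. The count is also described in two ways, so two analysts could use different denominators. Both an early date and a narrower case definition lower the denominator and raise the ICR. The Expected benefits section presents the survey as an objective measure of the second wave's impact, so these derived figures should be reproducible from the plan.

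**Working it through.** **1. What the two dates can change.** Write p for seroprevalence, N for the projected population, C(t) for cumulative reported cases t days before initiation, and D for deaths.

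- Infections = p × N. C does not appear.
- ICR = p × N / C(t). C appears only in the denominator.
- IFR = D / (p × N). C does not appear.

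The dates are 15 − 7 = 8 days apart. They give the ICR a range whose upper/lower ratio is C(7)/C(15), and they give infections none.

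**2. The plan's own figure.** The documents state no numeric range for infections, ICR or IFR. The only related figure is 1792 for ages 6-9 (Sample size, A] General population). With prevalence 30%, relative precision 10% and design effect 2:

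n = 2 × 1.96² × 0.70 / (0.30 × 0.10²) = 1792.7, which reproduces it.

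**3. Survey error left out.** The same planning inputs at the full sample of 28,000 give:

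- SE = √(2 × 0.30 × 0.70 / 28,000) = 0.00387
- half-width = 1.96 × 0.00387 = 0.76 points, or 0.76/30 = ±2.5% relative; upper/lower ratio 1.052.

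The round-3 result in the introduction, 24.1% (23.0 to 25.3), has limits 4.6% below and 5.0% above the estimate, ratio 1.10. If round 3 also had 28,000 participants (assumed; the plan says the overall size is kept), its SE is 2.3/(2 × 1.96) = 0.587 points. The implied design effect is 0.00587² / (0.241 × 0.759 / 28,000) = 5.3. At 30% prevalence that gives ±1.23 points, ±4.1% relative, ratio 1.086.

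**4. Effect on the ICR range.** This needs daily cases, which the documents do not give. I assume 25,000 to 400,000 a day and take C as the roughly 25 million reported by 29 May 2021. Date-only ratio: R = 1 + 8 × daily / 25 million. Survey ratio: r, from step 3. The widening factor compares log widths. Its lower value is √((ln r)² + (ln R)²) / ln R, and its upper value is (ln r + ln R) / ln R. Example at 50,000 a day with design effect 2: R = 1.016, ln R = 0.0159, ln r = 0.0506, factor 3.3 to 4.2.

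| Assumed cases a day | 8-day growth | Widening, design effect 2 | Widening, design effect 5.3 |
|---|---|---|---|
| 25,000 | 0.8% | 6.4 to 7.4 | 10.4 to 11.3 |
| 50,000 | 1.6% | 3.3 to 4.2 | 5.3 to 6.2 |
| 100,000 | 3.2% | 1.9 to 2.6 | 2.8 to 3.6 |
| 200,000 | 6.4% | 1.3 to 1.8 | 1.7 to 2.3 |
| 400,000 | 12.8% | 1.1 to 1.4 | 1.2 to 1.7 |

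**5. Anchor date.** From the dates in the introduction, round 2 ran 17 August to 22 September (37 days) and round 3 ran 18 December to 6 January (20 days). The midpoints fall (37 − 1)/2 = 18 and (20 − 1)/2 = 9.5 days after initiation. For blood drawn at mid-fieldwork, the nominal 7- and 15-day lags become 25 and 33 days (round-2 length) or 16.5 and 24.5 days (round-3 length). Cumulative cases cannot fall, so the count is understated and the ICR is pushed up. The size again depends on daily cases and on the round-4 fieldwork length, neither of which is given.

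**6. IFR.** One three-week lag yields one death date, hence one value and no range. Combining it with the 7- and 15-day lags would put deaths 21 − 7 = 14 and 21 − 15 = 6 days after the anchor, but the plan does not say that this is meant.

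**The case against.** The best defence is that the plausible range is a lag scenario, not a confidence interval. A CI for seroprevalence is planned, infections are a fixed multiple of it, and anyone can scale the limits; the plan nowhere rules this out. That stands in part: the fair criticism is that propagation is not stated, not that survey error is excluded. It does not rescue the sentence that attaches the case-date range to infections, nor does it say how the limits combine with the lags.

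A reader might infer that the ranges are several times too narrow. The documents do not support that as a general statement. It holds at lower daily counts and fails at high ones, and no daily count is given. Nor does it apply to all three quantities, since the dates affect only the ICR.

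A reader might also infer that an RT-PCR-only count inflates the ICR by some large multiple. No RT-PCR share is given. The sampling sentence concerns who may take part and does not define the denominator, so the RT-PCR wording may simply be loose. What stands is the inconsistency and its direction.

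On the anchor date, Study duration gives only two months including analysis, so the earlier rounds' lengths are a guide, not a figure for round 4. Finally, ICR and IFR are not among the stated objectives, which limits the consequence.

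**Conclusion.** The point holds as a defect in how the derived quantities are specified. The stated source of the range for infections cannot generate one, the seroprevalence CI has no stated route into infections, ICR or IFR, and the IFR range has no end points. Dating cases from initiation biases the ICR upward, and the denominator is described inconsistently. This is more than missing detail, because applying the rule as written gives ranges without sampling error and a denominator dated too early.

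The omitted survey error is modest: about ±2.5% relative (n = 28,000, 30% prevalence, design effect 2), or about ±5% judged by the round-3 interval. Adding it would widen the ICR range by a factor of about 1.1 to 11, depending on an assumed pace of 400,000 down to 25,000 cases a day at 25 million cumulative cases.

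It would be tempting to call survey error the dominant uncertainty; the documents do not show that. Positivity on either assay also captures vaccine-induced S1-RBD antibody, and the introduction reports 160 million people with at least one dose. That is a separate bias which a CI would not cover.

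**What to change.** Amend the Analysis plan, A] General population, as follows.

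1. Multiply the lower and upper limits of the design-based, test-adjusted seroprevalence CI by the population to give limits for infections. Divide these by the case count at each lag for the ICR. For the IFR, divide deaths by the limits for infections, so that the upper limit for infections gives the lower limit for IFR. Report estimate and limits at each lag, and reserve the two case dates for the ICR.
2. Count the 7- and 15-day case lags, and the death lag, from the median blood-collection date. State the resulting death date or dates, so that the end points of the IFR range are defined.
3. Use one case definition in the ICR: all officially reported cases, whether confirmed by RT-PCR or rapid antigen test.

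The cost is a few sentences and a short calculation, with no new survey data. The reported ranges become wider.
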